### Treatments used in the trial

2.4

#### Research drugs

2.4.1

The fish-oil emulsion employed in the study is commercialized as Omegaven, and the mixture emulsion of LCT/MCT is commercialized as Lipofundina

Lipids emulsions will be prepared at the Pharmacy Department with the same aseptic conditions used for NP (in a laminar flow cabinet). They will be delivered ready for administration in a multilayer bag, and will be stored and conserved in accordance with the normal procedures of the department of Pharmacy. The double blind will be facilitated by the identical galenic presentation of the lipid emulsions.

Emulsions will be dispensed when the trial recipe used in the University Hospital of Bellvitge is finalised.

#### Others concomitant treatments

2.4.2

During this trial both the patient's usual medication and any support medication needed during admission will be maintained as usual.

### Data collection

2.5

#### Demographic, pharmacological, clinical and analytical data

2.5.1

Demographics, clinical and analytical data generated following normal clinical practice will be collected and recorded in the Data Collection Logbook.

Demographic data: age, gender, body weight, height and BMI will be recorded.

Pharmacological data: any adjuvant chemotherapy received by a patient after trial treatment will be recorded specifying the treatment scheme.

##### Analytical data

2.5.1.1

-Inflammatory parameters: values of IL-6, RCP, TNF-α, IL-10, IL-8 y CD25 on days 0, 1, 3, 5 and 21 post-surgery will be recorded. These values have been selected according to what is reported in the literature in similar studies.^[19–25]^ Also, these same values will be recorded pre-operatively at the time surgical intervention is indicated to show the patient's baseline inflammatory status.-Nutritional parameters: albumin, prealbumin and lymphocytes at the time surgical intervention is indicated and on days 0, 1, 3, 5 and 21.-Hepatic parameters: total bilirubin, alanin-aminotranspherase, aspartat aminotranspherase, gammaglutamil transpherase and alkaline phosphatase at the time surgical intervention is indicated and on days 0, 1, 3, 5 and 21.-Safety: INR, prothrombin time and platelet count at the time surgical intervention is indicated and on days 0, 1, 3, 5 and 21.

The total number of blood extractions per patient will be 6.

Clinical data: the following data will be recorded:

-Post-surgery complications such as chylothorax, dehiscence, pneumonia and other infections.-Mortality: from the day of surgery to 1 year following surgery.-Nutritional support: the amount of EN received by each patient will be recorded to determinate total calories administered.

##### Quantification of cytokines

2.5.1.2

-Sample collection: Samples will be centrifugated at 700×*g* an hour post-extraction. Samples will be aliquoted and stored frozen at -80°C until analysis (1 year). Cytokine values will be determined by Enzyme-Linked ImmunoSorbent Assay (ELISA).

### Response assessment

2.6

#### Statistical analysis

2.6.1

Descriptive statistics will be employed for all collected variables data, such as baseline values for inflammatory, nutritional, hepatic and safety parameters, in frequency tables. For continuous variables, statistical descriptions will be used (n, average, standard deviation, value range and median), meanwhile grouped percentages will be used for categorical variables.

The main objective is to establish the difference between basal values of inflammatory parameters and values at day 5 post-randomization, and to assess differences between days 1, 3 and 21. The secondary objectives are to establish the difference between basal values of morbidity, safety and nutritional parameters and those values at day 5 post-randomization.

Significance will be calculated using Student's *t* test for matching data or Wilcoxon-test (non-parametric test) depending on whether normality can be assumed or not. To establish the differences among the 3 groups for the same period of time, Student's *t* test (parametric test) or Mann Whitney *U* test (non-parametric test) will be used, depending on whether normality can be assumed or not. For categorical variables, the chi-square test or the Fisher test will be used when necessary.

The significance level will be established with a 95% confidence interval (CI). Data will be processed with SPPS v 19.

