### Study objectives

2.1

The main objective of this study is:

To establish if the endovenous administration of ω-3 fatty-acid fish-oil lipid emulsions for 5 days in esophagectomized patients is effective in reducing inflammation – measured as seric concentration of interleukin-6 (IL-6) – compared to the administration of lipid emulsions of LCT/MCT. Additionally, to determine if doses of 0.8 g/kg/d are more effective than doses of 0.4 g/kg/d in the normalization of IL-6.

The secondary objectives aim to determine if the intravenous administration of ω-3 fatty-acid fish-oil lipid emulsions for 5 days in esophagectomized patients shows differences compared with the administration of LCT/MCT lipid emulsion with regard to:

Seric concentration of other inflammatory parameters: C-reactive protein, tumoral necrosis factor-α (TNF-α), interleukin-10 (IL-10), interleukin-8 (IL-8) and soluble interleukin-2 receptor. In addition, in the follow-up, whether these markers, alone or in combination, show equal or greater efficacy of effect on the inflammatory response compared to IL-6.Post-operative complications: suture dehiscence, chylotorax, pneumonia and other infections.Safety, measured as hepatic impairment and alterations in coagulation parameters.Nutritional parameters: albumin, prealbumin and lymphocytes.Mortality: evaluated at hospital admission and at 1 year post-surgical intervention.

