#### Patients recruitment, randomization and allocation

2.2.2

All patients allocated for EPG following medical criteria, and those who meet the inclusion criteria will be candidates to participate in the trial.

The surgical team will be responsible for communicating the possibility of participating in this trial when IC is obtained for the surgical intervention. IC for participation in this trial will be collected before randomization.

Subjects will be randomized to 3 groups (1:1:1) by a pharmaceutical researcher after recruitment by the surgical team:

Group A will receive 0.4 g/kg/d of fish-oil LE and 0.4 g/kg/d of a LE mixture LCT/MCT receiving a total dose of 0.8 g/kg/d of LE over 5 days post-surgery,Group B will receive 0.8 g/kg/d of fish-oil LE,And Group C will receive 0.8 g/kg/d of a LE mixture of LCT/MCT 50%.

This allocation will be blind for all patients and health personnel. The allocation sequence (computer-generated random numbers) will be generated by the pharmaceutical researcher and it will be performed by randomized blocks permutated with the block size defined at random. In the first step, blocks of size 3 with possible sequences ABC, ACB, CAB and CBA, and size 6 will be defined. In a second step the clusters will be randomized, and in a third step the sequences will be randomized within the blocks. This method ensures that the groups are balanced throughout the study, and that the researcher cannot predict the sequence. The pharmaceutical researcher will be responsible for patient assignation to the corresponding intervention group, and will also assign a numbered patient identification code for each patient in the trial. The composition of the emulsion administered to each patient will only be known by: the pharmaceutical researcher responsible for clinical trials, the pharmaceutical researcher who will validate its conduct, and the personnel who will conduct it.

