### Study variables

2.3

The main variable of this study is the variation of seric concentration levels of IL6 at randomization and on days 1, 3, 5, 21 post-surgery in esophagectomized patients receiving fish-oil lipid emulsions parenterally for 5 days compared with those receiving LCT/MCT emulsions.

The secondary variables will examine whether intravenous administration of fish-oil lipid emulsions instead of LCT/MCT for 5 days leads to differences from randomization and on days 1, 3, 5 and 21 post-randomization with respect to:

Seric concentrations of inflammatory markers: RCP, TNF-α, IL-10, IL-8 and soluble interleukin-2 receptor.Morbidity measured as post-operative complications: suture dehiscence, chylotorax, pneumonia and other infections.Safety measured as hepatic impairment (total bilirubin, alanin-aminotranspherase, aspartate-amino transpherase, gammaglutamil transpherase, alkaline phosphatase) and alteration in coagulation parameters (INR, prothrombin time, platelet count).Nutritional parameters: albumin, prealbumin and lymphocytes.Mortality measured for a year after surgical intervention.

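### The statistical section states the main objective as a before-after change with no comparator and follows it with paired tests, contrary to the between-arm IL-6 objective set elsewhere in the protocol

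*Protocol article*

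**What the plan says.** Section 2.1 (Study objectives) sets a comparative main objective: whether fish oil "is effective in reducing inflammation – measured as seric concentration of interleukin-6 (IL-6) – compared to the administration of lipid emulsions of LCT/MCT". It adds a dose question, "to determine if doses of 0.8 g/kg/d are more effective than doses of 0.4 g/kg/d in the normalization of IL-6". Section 2.3 (Study variables) defines the main variable as the variation in IL-6 in fish-oil patients "compared with those receiving LCT/MCT emulsions". Section 2.2.2 provides the randomisation for this: "Subjects will be randomized to 3 groups (1:1:1) by a pharmaceutical researcher".

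Section 2.6.1 (Statistical analysis) words the main objective differently: "The main objective is to establish the difference between basal values of inflammatory parameters and values at day 5 post-randomization". No arm is mentioned, and the single marker IL-6 has become inflammatory parameters in general. The next paragraph opens with the significance test, a Student's t "test for matching data or Wilcoxon-test (non-parametric test) depending on whether normality can be assumed or not". A further sentence gives two-sample t or Mann-Whitney U tests, introduced by "To establish the differences among the 3 groups for the same period of time".

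**The concern.** Two sections ask whether IL-6 differs between randomised arms. The section that governs the analysis asks whether markers differ between two times. These are different questions, and only the first uses the randomisation. The protocol's own abstract describes a strong inflammatory response to this surgery, so IL-6 can be expected to move over five days in every arm whatever emulsion is given. A paired test within an arm picks up that movement together with any treatment effect and cannot separate them.

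An analyst who follows 2.6.1 literally could report a significant fall in a fish-oil arm and none in control, and read that as efficacy. The analyst could equally find a significant change everywhere and learn nothing about treatment. Because two families of test are listed and neither is designated for the main objective, the choice stays open until the data are seen.

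**Working it through.** **Inputs from the protocol.** Three arms at 1:1:1, 33 patients, 80% power, 5% alpha and 10% losses (sections 2.2.2 and 2.2.3). The total of 33 cannot be reproduced, because no IL-6 difference or SD is given. Only the loss step can be checked: 30 × 1.1 = 33, while 30 / 0.9 = 33.3, rounded up to 34. Either way there are about 10 evaluable patients per arm.

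**Assumptions.** The protocol gives no IL-6 values. I take log IL-6 as normal, no treatment effect, the same baseline-to-day-5 shift in every arm, and a correlation r = 0.5 between the two times. The SD of the change is SD × √(2(1 − r)), which equals one SD at r = 0.5, so a shift in SD units is also the paired effect size.

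**Paired test within one arm.** The rejection probability p comes from the noncentral t distribution with 9 df and noncentrality shift × √10, two-sided 5%. With q = 1 − p and independent arms:

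- a given fish-oil arm significant and control not: p × q
- at least one of the two fish-oil arms significant and control not: (1 − q²) × q

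| Common shift (SD) | p per arm | p × q | (1 − q²) × q |
|---|---|---|---|
| 0 | 5% | 5% | 9% |
| 0.5 | 29% | 21% | 35% |
| 0.75 | 56% | 25% | 35% |
| 1.0 | 80% | 16% | 19% |
| 1.5 | 99% | 1% | 1% |
| 2.0 | about 100% | about 0% | about 0% |

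Example at 1.0 SD: p = 0.803 and q = 0.197, so (1 − 0.039) × 0.197 = 0.189. The last column equals q − q³, which peaks at q = 1/√3 = 0.577 with value 0.385. The range between 0.5 and 1 SD therefore runs from 19% to a little over 38%, with 35% at the 0.5 SD end.

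**Between-arm test under the same conditions.** In 40,000 simulated trials, the two-sample t test of change between group B and group C rejected about 5% of the time at every shift from 0 to 2 SD. The common shift cancels.

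**What baseline adjustment could add.** With 10 per arm, an unadjusted two-sample t test has 80% power at a standardised difference of 1.325. ANCOVA multiplies the residual variance by 1 − r², so the effective difference is 1.325 / √(1 − r²). Ranges below run from a two-arm model (17 df) to a three-arm model (26 df):

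- r = 0: 1.325, power 80% to 81%; no gain from the covariate
- r = 0.3: 1.325 / √0.91 = 1.389, power 83% to 85%
- r = 0.5: 1.325 / √0.75 = 1.530, power 90% to 91%

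This formula ignores chance baseline imbalance. Simulating the fitted model (6,000 runs) gave values about 1 to 3 points lower: 77% to 79%, 81% to 84%, and 88% to 90%.

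**The case against.** The best defence is that the document as a whole is comparative. Section 2.6.1 never calls the paired test the main analysis. It lists paired tests for differences over time and two-sample tests for differences among the three groups. The objective, the main variable and the between-group study behind the sample size all point to the second family. The article is condensed, and an analysis plan may exist. Most of this stands: a randomised comparison is planned, and an unadjusted two-sample test is valid. It does not remove the contradiction, because the only main objective stated in 2.6.1 has no comparator and the group tests are not tied to it. An analysis plan written from that section would inherit the conflict.

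Three stronger readings are tempting but not supported:

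- A reader might infer that the between-arm test ignores baseline IL-6. The text does not settle this. The main variable is described as a variation, and the wording on the same period could mean change over an interval as well as values at a visit.
- A reader might infer that a false contrast between arms is likely. That depends on the shift: it is about 1% at 1.5 SD. The protocol also states no rule that efficacy follows from significance in one arm and not in another.
- A reader might infer that choosing the test by a normality check costs much power. With the planned switch to Mann-Whitney, simulated power at 10 per arm under log-normal IL-6 (log-SD 0.6 to 1.0) was about 76% to 79%, against about 80% for a t test on the log scale. The loss is only about 2 to 4 points.

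**Conclusion.** The concern holds as an internal contradiction. Section 2.6.1 states a main objective that sections 2.1 and 2.3 do not share, pairs it with tests that cannot answer the comparative question, and leaves the between-arm test undesignated and its outcome (value or change) unstated. The protocol does not omit a between-arm comparison.

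Under no treatment effect, with 10 evaluable per arm and r = 0.5, a paired test in any one arm rejects 29% to 80% of the time for a common shift of 0.5 to 1 SD, and almost always at 1.5 SD or more. The between-arm test of change stays at 5%. The size of the shift and the correlation are assumptions. That a within-arm test cannot separate treatment from recovery does not depend on them.

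**What to change.** Rewrite the main-objective sentence in 2.6.1 so that the primary analysis is the between-arm difference in IL-6 at day 5, for the contrasts in section 2.1: fish oil versus LCT/MCT, and 0.8 versus 0.4 g/kg/d. Write each contrast out. Estimate it by ANCOVA on log IL-6 with log day-0 IL-6 as covariate, stating that the day-0 sample is taken before the infusion starts. Name IL-6 alone as the primary marker. Keep the within-arm paired tests as description, with no inference about treatment drawn from them.

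The cost is a change of wording and one degree of freedom. Section 2.5.1.1 already schedules IL-6 on days 0 and 5, so no extra patients or samples are needed. The power gain depends on a baseline correlation that the protocol does not give: none at r = 0, and by the formula above from 80% to 83–85% at r = 0.3 and to 90–91% at r = 0.5. The main reason for the change is that the analysis would then answer the stated question; added power is secondary.

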## Abstract

**Introduction::**

Esophagectomy is a major surgery with a high degree of catabolic and post-surgical inflammatory response accompanied by high morbidity and significant mortality. Post-surgical nutritional support via enteral administration of ω-3 fatty acids has been seen to be effective although its bad tolerance. There are few clinical trials with parenteral ω-3 fatty acids in these patients. We propose to investigate the effect of combining a parenteral fish oil lipid emulsion with the standard enteral nutrition (EN) support.

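### Section 2.6.1 words the main objective as a within-patient change from basal to day 5 and follows it with paired tests, although sections 2.1 and 2.3 pose a between-arm question

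*Protocol article*

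**What the plan says.** The protocol article describes the main objective in two ways.

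- **Section 2.1 (Study objectives)** is comparative. IL-6 under fish oil is to be judged "compared to the administration of lipid emulsions of LCT/MCT", and a second part is "to determine if doses of 0.8 g/kg/d are more effective than doses of 0.4 g/kg/d in the normalization of IL-6".
- **Section 2.3 (Study variables)** agrees. The main variable is the variation of IL-6 in patients "receiving fish-oil lipid emulsions parenterally for 5 days compared with those receiving LCT/MCT emulsions".
- **Section 2.2.3 (sample size)** also rests on a contrast between regimens: fish oil is assumed to act like the omission of ω-6 lipids in a cited study.
- **Section 2.6.1 (Statistical analysis)** restates the objective without a comparator: "The main objective is to establish the difference between basal values of inflammatory parameters and values at day 5 post-randomization". The next paragraph begins: "Significance will be calculated using Student's *t* test for matching data or Wilcoxon-test (non-parametric test) depending on whether normality can be assumed or not". Only then come the group comparisons: "To establish the differences among the 3 groups for the same period of time, Student's *t* test (parametric test) or Mann Whitney *U* test".

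Section 2.6.1 does not say which of the two kinds of test settles the main objective.

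**The concern.** A paired test compares each patient with himself or herself. It asks whether IL-6 differs between two time points and makes no use of the randomisation. The Abstract describes oesophagectomy as "major surgery with a high degree of catabolic and post-surgical inflammatory response", so IL-6 may well move over these days in every arm, whichever emulsion is infused. A small paired p-value in a fish-oil arm then describes recovery from surgery, not the emulsion.

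At stake is the link between the main objective and the p-value that supports it. As worded, the before-after objective fits the paired test and the group comparison has no stated priority. A report could therefore cite a significant within-arm change under fish oil as meeting the main objective, even if the control arm changed just as much.

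**Working it through.** **1. The plan's own figure.** Section 2.2.3 gives 33 patients for 80% power, 5% alpha and 10% losses, but no IL-6 difference or SD, so 33 cannot be reproduced from stated inputs. Working backwards with a two-sided comparison of two means, a standardised difference of 1.30 needs 2 × (1.960 + 0.842)² / 1.30² = 9.3, so 10 per arm and 30 in all. Adding 10% gives 30 × 1.1 = 33; dividing by 0.9 gives 34. This shows only that about 10 evaluable patients per arm is a sensible working number. It does not show which test was intended.

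**2. Inputs for the check.**
- Three arms, 1:1:1 (section 2.2.2), and 33 patients with 10% losses (section 2.2.3): 33 / 3 × 0.9 = 9.9, taken as n = 10 per arm.
- Alpha 5% (section 2.2.3), taken as two-sided because the article does not say.
- Assumed: no treatment effect, and the same mean change δ from basal to day 5 in all arms, measured in SDs of the within-patient change; normal changes; paired tests run by arm. The article gives no IL-6 mean, SD or change, so δ is shown as a range that includes zero.

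**3. Paired test in one fish-oil arm.** The statistic follows a noncentral t with n − 1 = 9 degrees of freedom and noncentrality δ√n. The critical value is 2.262.

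| δ (SD) | δ√10 | Paired test significant | Between-arm t test on change significant |
|---|---|---|---|
| 0 | 0 | 5% | about 5% |
| 0.5 | 1.58 | 29% | about 5% |
| 1.0 | 3.16 | 80% | about 5% |
| 1.5 | 4.74 | 99% | about 5% |

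A simulation of 40,000 trials per setting agrees: 5%, 30%, 81% and 99% for the paired test. With 11 per arm it gives 5%, 33%, 85% and 99%.

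**4. Between-arm test.** In the difference of mean changes the common course cancels: δ − δ = 0. The two-sample t test of group B against group C therefore keeps its level whatever δ is. The simulation gave 4.9% to 5.2%.

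**5. Comparing paired verdicts across arms.** If each arm's paired test is significant with probability p, then 'significant in B, not in C' arises by chance with probability p(1 − p). This is 0.293 × 0.707 = 21% at 0.5 SD and 0.803 × 0.197 = 16% at 1.0 SD. Such a pattern is not a test of B against C.

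**The case against.** The strongest reply is that section 2.6.1 does plan the right kind of test. The sentence after the paired tests provides two-sample comparisons among the three groups, sections 2.1 and 2.3 fix the comparative question, and sentence order is not a hierarchy. On that reading the basal-to-day-5 sentence only names the change and the key time point, and the group tests supply the comparison.

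Much of this stands. A reader might infer that efficacy will be judged on paired tests alone, or that significance in one arm and not another will be taken as an effect. The article says neither, and the percentages above are error rates of decision rules that it does not state.

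It is also fair that the size of the common change is unknown. If IL-6 were back near basal by day 5, the paired test would reject in close to 5% of trials. Section 2.5.1.1 lists both a pre-operative sample and a day 0 sample, and 2.6.1 does not say which one is basal.

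A third reply is that *normalisation* of IL-6 is partly a within-patient idea. That supports reporting within-patient changes. It does not let them answer the main objective, because section 2.1 asks whether one emulsion or dose does better than another.

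Finally, a condensed article may leave detail to the full protocol or SAP. That would cover a missing detail. Here the article states the main objective in a form that conflicts with its own sections 2.1 and 2.3.

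**Conclusion.** The point holds as a misalignment. Section 2.6.1 words the main objective as a before-after difference and attaches paired tests, while sections 2.1, 2.2.3 and 2.3 treat it as a contrast between regimens. The between-group tests are present but not named as decisive.

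The consequence is conditional. If a paired result were taken as deciding the objective, the false-positive rate would run from 5% with no common change to about 29%, 80% and 99% at common changes of 0.5, 1.0 and 1.5 SD, against about 5% for the between-arm test. These figures assume 10 patients per arm, normal changes, no treatment effect and the same mean change in all arms. The documents do not support the stronger statement that the trial will declare efficacy from paired tests.

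**What to change.** In section 2.6.1, or in the SAP:

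- Restate the main objective as the between-arm difference in IL-6 at day 5, as change from the baseline sample or adjusted for it, and name that sample.
- Say that this difference, with its 95% CI, decides the objective: fish oil versus LCT/MCT first, then 0.8 versus 0.4 g/kg/d. State whether fish oil means both arms together or each in turn.
- Keep within-arm changes as description, with means and CIs by arm, and do not use paired p-values as evidence of efficacy.
- Apply the same rule to the secondary markers.

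The cost is wording only. No extra patients, samples or visits are needed, and the between-group tests are already planned. What is given up is the use of paired p-values to support efficacy.

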##### Subject and/or treatment withdrawal criteria

2.2.1.1

Patients can voluntarily refuse to continue in the study at any time. In addition, presentation of any adverse effect related to the treatment will lead to a treatment withdrawal and to exclusion from the study.

All patients who present with surgical complications classifiable as grade IV of the Dindo-Clavien classification^[18]^ will be excluded from the study.

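### Liver, coagulation and nutritional values are defined and sampled on days 1, 3, 5 and 21, but the statistical section names only a basal-to-day-5 contrast for them

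*Protocol article*

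**What the plan says.** Study objectives (2.1) makes safety, meaning hepatic impairment and coagulation, a secondary objective to be compared between the emulsions. Nutrition is another.

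Study variables (2.3) sets the time points for all secondary variables together, asking whether fish oil instead of LCT/MCT "leads to differences from randomization and on days 1, 3, 5 and 21 post-randomization with respect to" the listed parameters. The list includes five liver parameters, three coagulation parameters and three nutritional parameters.

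Analytical data (2.5.1.1) schedules the samples to match. For the liver panel it lists "gammaglutamil transpherase and alkaline phosphatase at the time surgical intervention is indicated and on days 0, 1, 3, 5 and 21". Coagulation follows the same schedule ("INR, prothrombin time and platelet count at the time surgical intervention is indicated and on days 0, 1, 3, 5 and 21"), and so does nutrition ("albumin, prealbumin and lymphocytes at the time surgical intervention is indicated and on days 0, 1, 3, 5 and 21").

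Statistical analysis (2.6.1) treats the two sets of parameters differently in consecutive sentences. For the inflammatory parameters, the aim is the difference between basal values and "values at day 5 post-randomization, and to assess differences between days 1, 3 and 21". For the rest: "The secondary objectives are to establish the difference between basal values of morbidity, safety and nutritional parameters and those values at day 5 post-randomization".

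The withdrawal criteria (2.2.1.1) add that "presentation of any adverse effect related to the treatment will lead to a treatment withdrawal" and to exclusion from the study.

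**The concern.** The infusion lasts five days. A comparison of basal with day 5 looks at the end of exposure and nowhere else. If 2.6.1 is followed as written, three kinds of change fall outside the named safety comparison:

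- a liver-enzyme or INR rise on day 1 or 3 that has settled by day 5;
- a change that appears or persists after the infusion, seen at day 21;
- a change in a patient taken off the emulsion before day 5, who has no day-5 value after a full course and may have none at all if exclusion ends sampling.

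The third group matters most. Patients withdrawn for a treatment-related effect are the ones a safety comparison is meant to capture, and a day-5 contrast is the one most likely to leave them out. The trial could report no difference in liver or coagulation parameters at day 5 without having compared the arms on the days when a difference was visible. For nutrition, the day-21 value, the only one after the early post-operative days, has no named comparison.

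**Working it through.** There is no stated figure to reproduce, so the check sets the sections side by side and counts.

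| Parameters | Study variables (2.3) | Samples (2.5.1.1) | Named comparison (2.6.1) |
|---|---|---|---|
| Inflammatory | days 1, 3, 5, 21 | pre-operative, 0, 1, 3, 5, 21 | basal to day 5, plus days 1, 3, 21 |
| Liver | days 1, 3, 5, 21 | pre-operative, 0, 1, 3, 5, 21 | basal to day 5 |
| Coagulation | days 1, 3, 5, 21 | pre-operative, 0, 1, 3, 5, 21 | basal to day 5 |
| Nutrition | days 1, 3, 5, 21 | pre-operative, 0, 1, 3, 5, 21 | basal to day 5 |

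**Step 1: do definition and sampling agree?** Yes, for every row.

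**Step 2: does the analysis agree with the definition?** Yes for the inflammatory row. No for the other three.

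**Step 3: how much is affected?** The parameters listed in 2.3 are five liver (total bilirubin, ALT, AST, GGT, alkaline phosphatase), three coagulation (INR, prothrombin time, platelets) and three nutritional (albumin, prealbumin, lymphocytes).

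- Parameters: 5 + 3 + 3 = 11.
- Parameter-by-day combinations that 2.3 defines: 11 × 4 = 44.
- Combinations with a comparison named in 2.6.1: 11 × 1 = 11.
- Combinations without one: 44 − 11 = 33, or three of the four post-baseline days. This counts combinations and has nothing to do with the planned 33 patients.

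**Step 4: does other wording in 2.6.1 fill the gap?** In part. It promises descriptive statistics, including range and median, for every collected variable, and values from days 1, 3 and 21 are collected. A marked outlier could therefore show in a range if the tables are made by visit. A range does not give the number of patients affected, or show whether the same patient is abnormal at successive visits. The between-group tests are said to compare groups over a common period, but no days are named for safety or nutrition.

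**Step 5: what happens to early stoppers?** A patient withdrawn on day 2 or 3 can have a day-1 value and perhaps a day-3 value. Neither enters a basal-to-day-5 contrast. The article does not say whether sampling continues after exclusion, so how many day-5 values would be missing cannot be calculated.

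**The case against.** The strongest case against is that this is a condensed article, that its descriptive statistics cover all collected data, and that its between-group tests are not expressly confined to day 5. Harm to individuals is also followed in other ways. Serious adverse events are reported within one working day whatever their cause, and treatment-related effects are acted on patient by patient. On this view, one sentence is loosely worded and the analysis plan will supply the days.

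Much of this stands. A reader might infer that days 1, 3 and 21 are thrown away for safety and nutrition, or that harm to a single patient would go unseen. The document supports neither. No sentence discards those days, and adverse event reporting is separate from the laboratory comparison. A reader might also argue that a comparison of means in about 11 patients per arm (33 / 3) cannot pick out one or two badly affected patients. That is a fair remark about such tests, but it holds equally on day 1, 3 or 21, so it does not measure what is lost by choosing day 5. Cut-offs against laboratory reference limits and individual listings are usual content for an analysis plan, and their absence here is no fault.

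The objection does not remove the conflict. The article does fix a time point, and it fixes it differently from its own variable definition. The neighbouring sentence shows that the other days could be named when they were wanted. Serious adverse event reporting need not catch a laboratory rise that is not serious. The withdrawal rule removes patients from the study and does not report on them.

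**Conclusion.** The point holds as an inconsistency with a practical consequence. Study variables and Analytical data place safety and nutrition on four post-baseline days, while Statistical analysis names a comparison on one of them. The remaining three days, 33 of 44 parameter-by-day combinations, may be described but have no named comparison. A transient early rise, a change at day 21 or a change in a patient withdrawn before day 5 can therefore be missed in the stated safety comparison.

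This is worth correcting, but it does not undermine the trial. It concerns secondary objectives and leaves the IL-6 analysis untouched. The probability that a real effect would be missed cannot be given, because the document has no expected size or timing for liver or coagulation changes.

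The conclusion assumes that days counted from randomization in 2.3 and 2.6.1 are the same visits as the numbered sampling days in 2.5.1.1. It also assumes that basal means the pre-operative or the day-0 value; the count is the same for either.

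**What to change.** In 2.6.1, replace the day-5 contrast for safety and nutritional parameters with a comparison between arms on days 1, 3, 5 and 21, so that it matches 2.3. For the liver and coagulation values, also summarise by arm each patient's worst post-baseline value. State that patients who stop the emulsion early are included with whatever values they have. That statement is needed because adding days does not by itself bring back patients whom 2.2.1.1 excludes from the study. Cut-offs and listings can be left to the analysis plan.

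The cost is wording and a few tables, since every sample is already scheduled. Parameter-by-day comparisons rise from 11 to 44 for each pair of arms, and the worst-value summary adds eight (five liver, three coagulation). With that many and about 11 patients per arm, they should be labelled descriptive. A single small p-value among them should not be read as evidence of harm, nor its absence as evidence of safety.
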